### 2.14. Data Collection and Collation

The defecation diary (Figure 2) completed by the volunteers will be collected online daily, and the DASS-21 (Appendix 6) will be collected online as scheduled (see Table 1). One stool sample for the gut microbiome analysis and one for the metabolomics test will be collected from each volunteer on days 0 (preadministration period), 28 (administration period), and 42 (postadministration period); these samples will be stored separately and sent for tests at a temperature of −80°C in a special stool storage kit from Guangdong Longsee Company (https://www.longseemed.com).

An independent data management team (DMT) will be established to maintain and monitor study quality and safety. The data of individual characteristics, defecation diary entries (Figure 2), and DASS-21 data (Appendix 6) completed online by volunteers will be downloaded as Excel spreadsheets for further analysis. The gut microbiome and metabolomic data from stool samples will be examined by the Key Laboratory of Dairy Biotechnology and Engineering, Ministry of Education. All data will be submitted to the DMT for management and monitoring. The DMT will promptly analyse the data and contact collectors to resolve any uncertainty that occurs. All records that contain names or other personal information that could identify a participant, such as ID number or consent forms, will be stored separately from the study records. The database will be password protected by the DMT. The team will also have the authority to conduct an interim analysis or terminate the study's next step if the following situations occur: (1) if the probiotic does not affect the gut microbiome, then the study team will not conduct tests on the faecal metabolomes; and (2) if any severe adverse events related to the probiotics occur, the DMT will suggest terminating the study.

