### 2.6. Study Interventions

The *L. plantarum* P9 and placebo powders will be manufactured in parallel and independently by Research and Development Department, Jiangzhong Pharmaceutical Company Limited (Nanchang, China). Briefly, the preparation procedure consists of three steps: weighing, mixing, and packaging. *L. plantarum* P9 powder is composed of 20% maltodextrin, 20% orange powder, 20% maltitol, and 40% *L. plantarum* P9, while placebo powder consists of 60% maltodextrin, 20% orange powder, and 20% maltitol. Raw materials for *L. plantarum* P9 and placebo powders are mixed using a Hopper mixer (hit-400) and sealed into 2 g packages. The temperature is controlled at 25 ± 2°C, and the relative humidity is less than 65% during the three steps. In the study, when the product of *L. plantarum* P9 powder is manufactured, a randomized sample is sent to Jinhua Yinhe Biotechnology Co., Ltd. (https://yinhewdy168.foodmate.net/) for quality inspection. The activity of probiotics is greater than 67 billion colony-forming units (CFUs)/g.

The study will include three phases (Table 1), including a screening period (an observation period prior to treatment administration), an observation period during administration, and an observation period after administration. The interventions in each phase will be administered as follows:Period of screening (preadministration observation period) (days 14 to 0): in this phase, volunteers will not receive the intended interventions, i.e., probiotics and placebo. Eligibility screening will be performed as described during volunteer recruitment (Table 1).Observation period during administration (days 0 to 28): (1) Probiotics group: volunteers will take 1 package of *L. plantarum* P9 powder directly or with warm water (below 40°C) on a full stomach at a dose of 100 billion CFUs per day; if antibiotics must be taken, probiotics should be taken 2 hours later. (2) Placebo group: volunteers will take the placebo in the same manner as the probiotics group. The placebo contains no probiotics but has the same appearance, packaging, and taste as the *L. plantarum* P9 powder.All remaining probiotics or placebo (unused) and empty (used) packages will be collected at the end of this period to monitor compliance. During the study, both probiotics and placebo will be stored in a cool, dry place away from direct sunlight.Postadministration observation period (days 29 to 42): no probiotics or placebo will be taken.

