### 2.9. Secondary Outcomes

Based on the diary (Figure 2), the changes in the percentage of volunteers with a weekly mean frequency of CSBMs ≥3 [32, 54, 55], changes in the weekly mean frequency of spontaneous bowl movements (SBMs) [32, 54–56], weekly mean stool appearance score [53], weekly mean difficulty of passing stool score, and weekly percentage of volunteers who use auxiliary measures to assist with defecation (WPUAMA) will be evaluated each week from day 0 (week 0) to day 14 (week 2), day 28 (week 4), and day 42 (week 6). An SBM is defined as a bowel movement achieved without the use of any drugs or other auxiliary measures during the previous 24 hours [32, 54, 55] (Table 1).The Patient Assessment of Constipation Quality-of-Life (PAC-QOL) questionnaire (Appendix 5 [56, 57]) will be used to evaluate the QOL score on days 0, 14, 28, and 42.The Depression, Anxiety and Stress Questionnaire (DASS-21) [58, 59] (Appendix 6) will be completed online on days 0 (baseline), 14, 28, and 42 and used to assess the participants' emotional status (depression, anxiety, and stress) within the past week (Table 1).For the indicator of the gut microbiome, DNA will be extracted from the stool samples with the QIAamp Fast DNA Stool Mini Kit (Qiagen, Hilden, Germany) according to the manufacturer's instructions, and the quality of DNA will be examined using agarose gel electrophoresis and a NanoDrop spectrophotometer. Shotgun metagenomic sequencing will be performed on all samples using an Illumina HiSeq 2500 instrument. Libraries will be constructed from DNA fragments with a length of ∼300 bp; paired-end reads will be generated by sequencing 150 bp in the forward and reverse directions. Meanwhile, the metagenomic analysis will include several parts: the analysis of alpha diversity and beta diversity in each group to understand whether the differences in the microbiota compositions of groups are significant and a comparison of the taxonomic characteristics of the study group and the control group at the level of phylum, genus, and species to identify specific genes related to the individual differences of constipation. Metagenomic biological pathway analysis will be used to evaluate the effect of probiotics on the function of gut metagenomics in patients with constipation and to explore the metagenomic biological pathways contributing to the mechanism underlying the effect of probiotics on the treatment of constipation.For the indicator of the faecal metabolome, stool samples will be extracted using the protein precipitation method, and the supernatant will be transferred to sample vials for LC-MS/MS analysis. The original data will be subjected to peak alignment, retention time correction, and peak area extraction using the XCMS-Plus program. The structure of metabolites will be identified by accurate mass matching (<5 ppm) and two-level spectrum matching, and the METLIN database will be retrieved. We will then delete data with missing values > 50% in the group, normalize the data, and conduct multidimensional statistical analysis, including unsupervised principal component analysis (PCA), supervised partial least squares discriminant analysis (PLS-DA), and potential differentially abundant metabolite analysis. The metabolomic analysis might further identify the potential differentially abundant metabolites of probiotics in the treatment of constipation, and a correlation analysis between the gut microbiota and metabolites will be performed.

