We optimize the methodology from the following aspects: ① The general principle for a high-quality RCT is strictly obeyed through the participation of third-party independent companies or the DMT, including randomization, parallel control, blinding, allocation concealment, combination of ITT and PP analyses, consideration of withdrawals or dropouts, replication (enough observed study subjects), and other factors. ② The sample size (100 for each group) is obtained based on the expected difference in weekly frequency of CSBMs between the treatment group and control group, which is sufficient to ensure the reliability and accuracy of the results. The sample sizes in 33 of the 35 previous RCTs are dozens or even several participants, which is probably not sufficient to obtain an accurate result. ③ The latest Rome criteria (Rome IV for the present RCT) are suggested for the diagnosis of chronic constipation to avoid any other self-definition by researchers. ④ Multidimensional outcomes have been observed in the present RCT, including improvements in clinical symptoms, QOL score, emotional status score, and modifications in the gut microbiome and faecal metabolome, to produce a chain of evidence from causal improvements in metagenomic and metabolomic data to clinical symptoms and then to the emotional state and QOL. The outcomes are measured using accepted methods, e.g., BSFS [53], PAC-QOL [57], DASS-21 [58], next-generation sequencing, and LC–MS/MS analysis. Thus, the effects of probiotics on chronic constipation in the present study are more reliable and explainable. ⑤ Other key parameters, such as the study stage and duration, are also suggested.

In addition, the protocol is conducted to prove its feasibility and scientificity by studying the effects of *L. plantarum* P9 on chronic constipation. The study is articulated with a clear testable hypothesis stating that *L. plantarum* P9 improves the clinical symptoms and patient QOL by modifying the intestinal flora. Additionally, the safety of *L. plantarum* P9 will be assessed.

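### The day-28 metagenomic comparison counts the product's own DNA, so a species-level difference between arms is expected from dosing alone

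*Protocol article*

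**What the plan says.** - **Dosing (2.6).** The treatment phase is given as "Observation period during administration (days 0 to 28", and the powder is taken "on a full stomach at a dose of 100 billion CFUs per day". Dosing then stops: "Postadministration observation period (days 29 to 42): no probiotics or placebo will be taken".
- **Sampling (2.14, Table 1).** The stool samples for microbiome and metabolome "will be collected from each volunteer on days 0 (preadministration period), 28 (administration period), and 42 (postadministration period". The article itself labels day 28 as on treatment.
- **Assay (2.9).** DNA is extracted from stool, and "Shotgun metagenomic sequencing will be performed on all samples using an Illumina HiSeq 2500 instrument".
- **Comparison (2.9, 2.15).** The plan covers alpha and beta diversity, biological pathways and "a comparison of the taxonomic characteristics of the study group and the control group at the level of phylum, genus, and species". Section 2.15 adds t, Wilcoxon and Kruskal-Wallis tests with Benjamini-Hochberg correction, and adonis with 999 permutations. No distance measure is named, and P9 or its species is not set apart.
- **Hypothesis (3. Discussion).** P9 "improves the clinical symptoms and patient QOL by modifying the intestinal flora".

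**The concern.** Sequencing of whole-stool DNA counts swallowed bacteria in transit together with resident ones. At day 28 one arm is swallowing P9 and the other is not, so the administered organism is itself an outcome variable in the comparison between arms. A difference in L. plantarum then shows that volunteers took the powder. It does not show that their own flora changed.

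At stake is the flora link in the stated mechanism. If a day-28 arm difference is reported without separating the product from the residents, a reader cannot tell exposure from modification.

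**Working it through.** **1. Timing.** Day 0 is before dosing. Day 28 is inside the dosing window of 2.6. Day 42 is 42 − 28 = 14 days after the last dosing day.

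**2. Dose.** Section 2.6 gives 2 g packages and says "The activity of probiotics is greater than 67 billion colony-forming units (CFUs)/g". If that is per gram of finished powder: 2 × 67×10^9 = 1.34×10^11. If it is per gram of the P9 ingredient (40% of the powder): 2 × 0.4 × 67×10^9 = 5.4×10^10. The stated 100 billion per day has the same order of magnitude on either reading, and the point needs no more than that.

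**3. P9 share of stool bacteria.** Share = D·r / (D·r + B), with D = 10^11 per day. The documents do not give B (faecal bacteria per day, assumed 10^12 to 10^14) or r (recovery of P9 DNA, assumed 1% to 100%).
- Highest: 10^11 / (10^11 + 10^12) = 9.1%.
- Lowest: 10^9 / (10^9 + 10^14) = 0.001%.
- B = 10^13: 0.10% at r = 10%, and 0.99% at r = 100%.

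A share near 1% is possible but not assured.

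**4. Simulation with unchanged resident flora.** There were 100 volunteers per arm (2.12), and resident flora was drawn from one distribution for both arms. P9 reads were added only in the probiotic arm. Assumptions that are not in the documents: 150 resident species, 5 million reads per sample, P9 absent in placebo, P9 share log-normal between volunteers (log SD 1) around the median shown, 199 permutations, and 60 runs per row. Entries are the percentage of runs positive at 0.05 (species tests after Benjamini-Hochberg).

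| Median P9 share | Any species | P9 the only species hit | Bray-Curtis adonis | Log-ratio adonis | Shannon | Richness | Any species, P9 removed | Bray-Curtis adonis, P9 removed |
|---|---|---|---|---|---|---|---|---|
| 0 | 3 | 0 | 7 | 0 | 3 | 2 | 3 | 5 |
| 0.01% | 100 | 93 | 5 | 100 | 5 | 17 | 7 | 2 |
| 0.1% | 100 | 95 | 7 | 100 | 12 | 15 | 2 | 7 |
| 1% | 100 | 90 | 88 | 100 | 2 | 28 | 2 | 8 |
| 5% | 100 | 93 | 100 | 100 | 2 | 25 | 3 | 3 |
| 10% | 100 | 90 | 100 | 100 | 10 | 23 | 3 | 8 |

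With 60 runs, a true rate of 5% has a standard error of √(0.05 × 0.95 / 60) = 2.8 percentage points. The values after removal (2-8%) therefore agree with the nominal level.

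**5. Reading the table.**
- The species test reacts even at 0.01%, because that share is 0.0001 × 5,000,000 = 500 reads against none in placebo.
- P9 is the only species flagged in 90-95% of runs, so the tests of other species stay close to their nominal behaviour.
- Bray-Curtis adonis responds only near 1% or above.
- Shannon diversity shows no trend, and richness moves modestly (15-28%).

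**6. Limits.** Shares below 0.01% and the genus, phylum and pathway comparisons were not simulated. Log-ratio adonis, Shannon diversity and richness were not rerun after removal of P9. For pathways the argument is by reasoning only: genes carried by P9 count towards them.

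**The case against.** **Handling of product reads may be set out elsewhere.** A journal article condenses a fuller protocol, and no analysis plan is shown. Silence on a filtering step is not in itself an error, and this stands. But the article does fix the visits, the assay and the comparisons, and following them as written gives a near-automatic species difference. The point is a change to the stated method.

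**The species comparison names its hits.** A result that shows only L. plantarum is visible as such, and other species are tested alongside it. This also stands. A reader might infer that the day-28 analysis cannot tell the hypothesis from its null at all. The documents do not support that: the tests of other species remain informative, and Shannon diversity barely moves.

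**P9 DNA cannot confirm the hypothesis.** A reader might infer that it could. The hypothesis is clinical and quality-of-life benefit by way of the flora, so product DNA bears on the flora link only.

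**An off-product sample exists.** Day 42 is in 2.14 and Table 1, so the design does not lack one, although the article gives it no particular role. It would be tempting to make a change that outlasts dosing the deciding test. The hypothesis does not require persistence, and the Background counts delivery of beneficial organisms to the host as part of the rationale. That stronger demand falls.

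**The P9 share is assumed.** It is, over a wide range. The species-level result held at every share simulated, while the Bray-Curtis result depends on the share. If placebo volunteers carry L. plantarum, the species difference would be smaller. Section 2.7 bars other probiotics and foods that contain them, which limits this but does not exclude it.

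**Conclusion.** The point holds in a limited form. At day 28 a difference between arms in L. plantarum and in log-ratio distances is expected from dosing alone (100% of runs at median shares of 0.01% to 10%). A Bray-Curtis difference is expected only if P9 is about 1% of reads or more (88% at 1%, 100% at 5% and above, but 5-7% at 0.1% and below). Such a difference on its own cannot support the statement that resident flora was modified.

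These sizes rest on the assumed stool counts, DNA recovery, community structure and absence of P9 in placebo. The dosing days, sampling days, dose and planned comparisons come from the article. The issue concerns a secondary outcome and one link of the mechanism. The analysis of complete spontaneous bowel movements is untouched.

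Section 2.14 also makes metabolome testing depend on a microbiome effect. A reader might infer that product reads will decide that step. The article does not say which visit or measure it uses, so that inference is not supported.

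**What to change.** In 2.9 and 2.15:
1. Report P9 abundance (or L. plantarum, if the strain cannot be resolved) separately by arm and visit, as a measure of exposure.
2. Run the diversity, taxonomic and pathway comparisons between arms with P9-assigned reads removed and the data renormalised, using the same filter in both arms and at all visits. Present them beside the unfiltered analysis.
3. Base any statement that resident flora was modified on the P9-removed comparison.
4. Report the off-product day-42 sample as supportive evidence, not as a required test of persistence.

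The cost is one bioinformatic filtering step on data already planned, plus wording. No new samples or visits are needed. Two downsides should be stated: the filter may also remove resident L. plantarum, and the microbiome result may look less striking.

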### 2.15. Statistical Analysis

The intention-to-treat (ITT) analysis will be conducted between the two groups. Then, the following four data sets will be used for the per-protocol (PP) analysis: (1) the data from all participants who completed the follow-up and (2) a subgroup analysis regarding levels of compliance (≥80%, 60–80%, and <60%) to validate the robustness of the results. The hypothesis will be tested using the methods described below during the ITT and PP analyses.

First, the Wilcoxon signed-rank sum test will be used for the outcome measures, including the weekly mean frequency of CSBMs, weekly mean stool appearance score, weekly mean difficulty of passing stool score, weekly mean frequency of SBMs, QOL score, and emotional status score, at each observation point to analyse the intergroup differences in each outcome measure. The chi-square (*χ*^2^) test will be used for the outcome measures, namely, the percentage of volunteers with a weekly mean frequency of CSBMs ≥3 and WPUAMA, at each observation point. In the analyses, the *P* value indicating statistical significance will be set to 0.05.

Then, the Kruskal–Wallis rank sum test will be used for multiple comparisons of outcome measures, including the weekly mean frequency of CSBMs, weekly mean stool appearance score, weekly mean difficulty of passing stool score, weekly mean frequency of SBMs, QOL score, and emotional status score, and the *χ*^2^ test will be used for multiple comparisons of outcome measures, including percentage of volunteers with a weekly mean frequency of CSBMs ≥3 and WPUAMA, at each observation point to identify the intragroup changing trends in consecutive phases, namely, pre-, during, and postprobiotic administration. In the analyses, the *P* value indicating statistical significance will be adjusted to 0.05/[*k* (*k* −1)/2], where *k* is the number of sample groups included in the comparison.

In addition, the statistical analyses of metagenomic and metabolomic data will be performed using *R* software (v.4.0.2) and Adobe Illustrator. PCA and PLS-DA will be performed and visualized using the *R* packages vegan, ggplot, and ggpubr, and the adonis *P* value will be generated based on 999 permutations. The *t*-test, Wilcoxon test, and Kruskal–Wallis test will be used to evaluate differences in variables between and within groups; *P* values will be corrected for multiple testing using the Benjamini–Hochberg procedure. Meanwhile, Pearson's and Spearman's correlation coefficients will be calculated to analyse the correlations between different indicators in clinical, metagenomic, and metabolomic data.

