## 2. Methods and Design

### 2.1. Design

This study is a randomized, double-blind, placebo-controlled clinical trial conducted in Nanchang, China, and volunteers may receive the intervention (oral probiotics or placebo) in their own homes. The protocol was prospectively registered at the Chinese Clinical Trial Registry (ChiCTR) (NO. ChiCTR2000038396) (Appendix 1) and approved by the Ethics Committee of the First Affiliated Hospital of Nanchang University (Approval Number: IIT [2020], Clinical Ethics Review NO. 004) (Appendix 2). This manuscript is prepared according to the Standard Protocol Items: Recommendations for Interventional Trials (SPIRIT) [51]. The flowchart of the trial process is provided in Figure 1.

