### 2.5. Randomization and Blinding

Eligible volunteers will be assigned a unique serial number (e.g., 001, 002, 003, 004, 005……). The unique number will be used as the volunteers' ID throughout the study period to guarantee anonymity and confidentiality. For each of these unique numbers, a random sequence will be generated by the computer software *R* 4.1.0 and used to randomly assign the unique number (participant) to the probiotic group or the placebo group. During the study, the volunteer's treatment distributors, data collectors, and data analysts will be blinded to the randomization sequence. The randomization sequence will be maintained by an independent project administrator and will only be unblinded in the case of major safety issues or when performing the interim and final data analyses. Moreover, an independent project administrator will label the probiotics or placebo packages with unique numbers corresponding to random sequences in advance to achieve allocation concealment. During the period of administration, the distributor will distribute the treatment packages according to the unique number that corresponds to each participant.

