### 2.8. Primary Outcome

A defecation diary developed with reference to the literature [32, 53–56] will be completed daily online by the participants (Figure 2). Based on the diary, the changes in primary and some of the secondary outcomes from day 0 (week 0) to day 42 (week 6) will be evaluated.The primary outcome measure is the weekly mean frequency of complete spontaneous bowel movements (CSBMs) [32, 54, 55].

A CSBM is defined as the ability to achieve a complete bowel movement without the use of any drugs or other auxiliary measures during the previous 24 hours. Based on the diary (Figure 2), the weekly mean frequency of CSBMs from day 0 (week 0) to day 14 (week 2), day 28 (week 4), and day 42 (week 6) will be evaluated [32, 54, 55] (Table 1).

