### 2.12. Sample Size

This study is a clinical trial during which volunteers will consume a sample medication or placebo for 28 days and will be followed up for 42 days. The primary outcome measure is the weekly frequency of CSBMs. The expected weekly frequencies of CSBMs on day 28 are 1.1 in the control group and 4.1 in the probiotic group, with a between-group difference of 3. Given a standard deviation *S* = 6, *α* = 0.05, and *β* = 0.20, the sample size should be at least 63 volunteers per group, as calculated with the formula for statistically significant effectiveness. After considering the drop-out rate (20% or lower), the sample size should be 76 or more participants per group. The final sample size will be 100 participants per group for a total of 200 volunteers.

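### The between-arm test of the primary outcome is named as the Wilcoxon signed-rank test, which needs paired data, but the two randomised arms are independent

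*Protocol article*

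**What the plan says.** Section 2.15 (Statistical Analysis) opens its hypothesis tests with: "First, the Wilcoxon signed-rank sum test will be used for the outcome measures, including the weekly mean frequency of CSBMs". The sentence goes on to list five more outcomes: stool appearance, difficulty of passing stool, SBM frequency, quality of life and emotional status. It gives the purpose as "at each observation point to analyse the intergroup differences in each outcome measure". Section 2.8 makes weekly mean CSBM frequency the primary outcome.

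The design is a parallel-group one. Section 2.5 says that a computer-generated sequence is "used to randomly assign the unique number (participant) to the probiotic group or the placebo group". Neither that section nor section 2.1 mentions matching or pairing.

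The other tests in section 2.15 have other jobs:

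- The chi-square test is for the two percentage outcomes.
- The Kruskal-Wallis test is used "to identify the intragroup changing trends in consecutive phases, namely, pre-, during, and postprobiotic administration".
- The last paragraph, on metagenomic and metabolomic data, says: "The *t*-test, Wilcoxon test, and Kruskal–Wallis test will be used to evaluate differences in variables between and within groups". It does not say which Wilcoxon test, and it does not cover the clinical outcomes.

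**The concern.** The signed-rank test ranks the differences within pairs, or the deviations of one sample from a fixed value. At a given visit a volunteer on probiotic has no partner on placebo, so there are no such differences. The plan therefore ties the primary between-arm comparison to a test that the design cannot supply with data.

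This is the confirmatory test of the trial. Taken literally, it is either undefined (unequal arms) or not reproducible (equal arms, with the answer depending on how volunteers are paired). An analyst might instead turn to the test's only natural use here, change from day 0 within each arm. That does not compare the arms, and a placebo response or regression to the mean shared by both would look like an effect.

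**Working it through.** **1. What the sample size assumes.** Inputs from section 2.12: expected weekly CSBM frequencies of "1.1 in the control group and 4.1 in the probiotic group, with a between-group difference of 3", SD 6, α = 0.05, β = 0.20. The formula for two independent means, two-sided, is

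n = 2 × (z₀.₉₇₅ + z₀.₈₀)² × SD² / δ² = 2 × (1.960 + 0.842)² × 36 / 9 = 62.8, rounded up to 63 per group.

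This is the protocol's own figure. The design calculation treats the arms as unpaired, which does not match a paired test.

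**2. Can the named test be run?** With 78 values in one arm and 80 in the other, the paired test stops with an error. Section 2.12 allows for dropout of up to 20%, so unequal arms at a visit are likely.

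**3. If the arms happen to be equal.** Independent arms of 80 (100 less 20%) were simulated and then paired at random 2,000 times. The distributions are illustrative.

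| Simulated data | Rank-sum p | Signed-rank p over pairings |
|---|---|---|
| Normal, means 1.1 and 3.0, SD 6 | 0.148 | 0.018 to 0.446 (2.45% of pairings below 0.05) |
| Skewed counts (gamma-Poisson), means 1.1 and 1.7, SD 1.8 | 0.17 | 0.11 to 0.63 |
| Normal, protocol planning values 1.1 and 4.1, SD 6 | 0.002 | 0.0002 to 0.020 |

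The first row falls on both sides of 0.05. In the other two rows the p-value moves but the conclusion does not.

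**4. Error rate and power with one pairing fixed in advance, 80 per arm.**

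- Type I error is 4.5% for skewed counts (mean 1.1, SD 1.8) and 5.2% for normal data, so it is not inflated.
- At the protocol's planning values with normal data, both tests have power of about 87 to 88%.
- With skewed counts, means 1.1 and 1.9, the signed-rank test has about 88 to 90% power and the rank-sum test 97 to 98%.

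**5. If the test were run within arms.** Take a shift of 0.3 SD common to both arms, correlation 0.5 between visits and no treatment effect. The SD of the change is √(2 × (1 − 0.5)) = 1, in units of the outcome SD. With 80 per arm and an efficiency of 0.955, the expected test statistic is 0.3 × √(80 × 0.955) = 2.62. The chance of significance is about Φ(2.62 − 1.96) = Φ(0.66) ≈ 75%. Simulation gave about 73%.

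**6. Does the correct test need more volunteers?** Divide 62.8 by the asymptotic efficiency of the rank-sum test relative to the t-test:

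- Normal data (3/π = 0.955): 62.8 / 0.955 = 65.8, so 66 per group. After 20% dropout, 66 / 0.8 = 82.5, so 83.
- Lower bound (0.864): 62.8 / 0.864 = 72.7, so 73 per group. After dropout, 73 / 0.8 = 91.3, so 92.

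Both are below the planned 100. With 80 evaluable per group, power is about 87% and 84% respectively.

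**7. The neighbouring test.** Kruskal-Wallis assumes independent groups, but section 2.15 applies it to repeated measurements on the same volunteers. In simulation (100 volunteers, four time points, no change over time) it rejected in about 0.4% of runs at a within-person correlation of 0.5 and in none at 0.7, against a nominal 5%. The Friedman test stayed near 5%.

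**The case against.** The best defence is that this is a naming slip. The printed name is a hybrid of signed-rank and rank sum, the stated purpose is a comparison between groups, the next paragraph calls Kruskal-Wallis a rank sum test, and the sample size assumes independent means. An analyst with two unpaired arms of unequal size would probably run the rank-sum test, because software refuses the paired one.

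That is plausible, but it does not make the text right. The word signed identifies the paired test. The same section also makes the opposite mistake by giving Kruskal-Wallis to within-person trends, so real confusion between paired and unpaired methods cannot be ruled out.

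Three points about size do stand:

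- The within-arm figure describes a use that section 2.15 does not assign to this test. It is a conditional risk only.
- With a pairing fixed in advance, the type I error is sound, and at the protocol's own planning values no power is lost. The loss appears only under the assumed skewed counts with a smaller effect.
- Instability across pairings changes the conclusion mainly in borderline results.

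It is also fair that an effect estimate with its interval, and the exact Wilcoxon test for the omics data, may be left to an analysis plan that is not shown.

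**Conclusion.** The concern holds. The protocol names a specific test for the primary between-arm comparison, and that test does not fit two independent arms. No other part of the document supplies a valid one. This is an error in what is written, not a missing detail.

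The conclusion follows from the design and the wording and needs no simulation. The simulated p-values and powers only illustrate the consequences and rest on the assumed distributions. The defect is that the test cannot handle unequal arms and that its result depends on an arbitrary pairing; inflated type I error is not part of it. Because it concerns the confirmatory test, it must be corrected before unblinding, even if the cause is only a misprint.

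**What to change.** In section 2.15, replace the signed-rank test with the Wilcoxon rank-sum (Mann-Whitney U) test for two independent samples for all intergroup comparisons of the six listed outcomes. Reserve the signed-rank test for paired changes within an arm.

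Two additions are advisable, here or in the analysis plan: report the Hodges-Lehmann difference with its 95% confidence interval, and state which Wilcoxon test is meant in the metagenomic and metabolomic paragraph. While the section is open, the within-arm Kruskal-Wallis test should give way to a method for repeated measurements, such as Friedman.

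The core change is one sentence. It needs no new data, no change in sample size and nothing from participants.
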